### **Detailed Description of Study Population**

The study population will be children aged 3-59 months living in the districts of Ouelessebougou. The study will include up to eight sub-districts in the districts of Ouelessebougou estimated and up to 10,800 children less than five years of age.

#### ***Community consent***

The objectives of the study and the method to conduct the study will be discussed with the Ministry of Health and district health officials prior to its commencement. Community approval will be sought through meetings with leaders of the study communities at the sub-district level as well as the village level. During these meetings the study procedures (including information on SMC delivery) will be explained to the leaders. There will be no special advertisement for a particular method. Parents will be informed to make the children in the target age group available at home in villages randomized to door to door delivery or to bring them to a specified fixed point in the villages randomized to fixed point delivery. Leaders will have the opportunity to ask questions and provide input on the best ways to encourage community participation. They will be asked together with the community health workers to pass the information to members of the communities.

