#### ***Census and randomization***

Once community consent to the trial is obtained, a household census will be conducted and all households within the study areas with children under 5 years of age will be identified. At the time of census, a preliminary screening of potentially eligible children will be undertaken. Eligible children will be identified and written informed consent will be obtained from their caretakers for their inclusion in the trial. Children entered into the trial will be assigned a unique ID number and their demographic data (date of birth and/or age, and gender) will be collected.

The census will be updated at each SMC round and potentially eligible participants (such as children who did not reach the age of three months during the previous round) will be identified and screened for eligibility and enter into the study. This updated census will collect information on migration and death of children enrolled into the study for precise estimation of person-time of follow-up.

The unit of randomization will be village and all eligible children in a village will be allocated to the same study arm (DDD+ DOT or DDD+NDOT or FPD+ DOT or FPD + NDOT) to avoid confusion in Year 1. Villages in the selected sub-districts will be randomized at 1:1 ratio to receive either a door –to-door delivery (DDD) or fixed point distribution (FPD) of SMC. They will also be randomized to receive SMC as directly observed therapy (DOT) or a non-directly observed therapy (NDOT). In Year 2, villages in the two newly randomly selected districts will be randomized into two groups to receive either three or four rounds of SMC.

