### **6.3 Processus de consentement**

#### **6.3.1 Permission Communautaire**

Les objectifs de l'étude et la méthode de réalisation de l'étude seront discutés avec le Ministère de la Santé et les autorités sanitaires du district avant le démarrage. L'approbation de la communauté sera recherchée à travers des réunions avec les dirigeants des localités de l'étude au niveau des aires de santé ainsi qu'au niveau des villages. Au cours de ces réunions, les procédures de l'étude (y compris des informations sur la mise en œuvre de la CPS) seront expliquées aux dirigeants. Le processus de permission communautaire pourra suivre les étapes suivantes :

- Explications et éclaircissements aux leaders, y compris le chef du village et les anciens sur les objectifs, les procédures ainsi que les risques pour les sujets de l'étude.
- Donner du temps aux leaders pour communiquer avec les membres de la communauté et nous informer sur toutes questions ou préoccupations de la communauté.
- Approfondir l'explication du protocole aux différents chefs de famille.

Il n'y aura pas de publicité spéciale pour une méthode particulière. Les parents seront informés et leur consentement sera demandé afin de faciliter la disponibilité des enfants du groupe d'âge cible à la maison dans les villages randomisés pour la distribution à domicile ou les conduire dans un lieu fixe qui sera déterminé dans les villages randomisés pour la distribution au point fixe. Les dirigeants auront l'occasion de poser des questions et donner leurs avis sur les meilleurs moyens d'encourager la participation de la communauté. Ils seront invités ainsi que les agents de santé communautaires à transmettre les informations aux membres des communautés.

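### Nothing keeps a village's delivery method from caregivers before individual consent, and the coverage denominator is not fixed, so Year 1 coverage can be computed on arm-dependent denominators

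*Protocol*

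**What the plan says.** **Community step.** In the English protocol, section 4, Community consent: "Community approval will be sought through meetings with leaders of the study communities at the sub-district level as well as the village level". The same paragraph covers parents: "Parents will be informed to make the children in the target age group available at home in villages randomized to door to door delivery". In the other villages, children are to be taken to a fixed point. Of the leaders it says: "They will be asked together with the community health workers to pass the information to members of the communities". Section 5.D, Community Consent, lists an explanation of the protocol to family heads as the last community step. The French section 6.3.1 goes further and attaches the parents' agreement to the method: "leur consentement sera demandé afin de faciliter la disponibilité des enfants du groupe d'âge cible à la maison dans les villages randomisés".

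**Census and individual consent.** Section 4, Census and randomization: "Once community consent to the trial is obtained, a household census will be conducted and all households within the study areas" with young children are to be identified. Then: "Eligible children will be identified and written informed consent will be obtained from their caretakers for their inclusion in the trial". Under Inclusion and exclusion criteria, a child is eligible only if the parent consents. The list stays open: "The census will be updated at each SMC round and potentially eligible participants" are then screened and entered.

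**French consent text.** Sections 6.2 and 6.3.2 provide for oral consent before SMC is given and separate written consent for children selected for the cross-sectional surveys.

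**Outcome.** Section 3.B defines Year 1 coverage as the proportion of children who received all three doses at all three rounds. Follow-up and measurement of outcomes says it is measured in the end-of-season survey of a random sample, from caregiver interview and the SMC card. Neither place says whether the sample is drawn from all listed eligible children or only from those whose caregivers consented.

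**The concern.** This is an open cluster trial in which individuals are recruited separately from the randomisation of villages. If caregivers know the method when they consent, the children who enter can differ by arm even though the villages were randomised properly.

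The outcome makes this worse than usual. Coverage measures uptake, and a caregiver's readiness to consent is closely related to readiness to complete three rounds. If reluctant families drop out of the denominator mainly where the method is demanding, coverage there looks better than it is. The demanding arms are the fixed-point ones, above all fixed-point delivery with directly observed treatment.

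Year 1 coverage is the primary basis for choosing the delivery method, which is then used in Years 2 and 3. A later analysis plan cannot recover families who were never recorded, so the order of events has to be settled in the protocol.

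**Working it through.** **1. Order of events**

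| Source | What it supports |
|---|---|
| Community consent (English) and 6.3.1 (French) | Method-specific information to parents belongs to the community step; in French, so does their agreement |
| Census and randomization, opening sentence | Census and individual consent follow the community step |
| Census and randomization, later paragraph | Describes village randomisation after census and consent |
| Overall design; row order of Table 1 | Mention randomisation before the census; weak evidence, since neither gives dates |
| Updating at each round | Later entrants are consented with the arm already in force |
| French 6.2 and 6.3.2 | Written consent to the end-of-season survey follows a season in the arm |

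The last two rows do not depend on when the first meetings take place. No row contains a safeguard.

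**2. Burden by arm** (section 4, Interventions; three rounds, three treatment days each)

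- Fixed point, directly observed: 3 × 3 = 9 attendances per season.
- Fixed point, not directly observed: 3 × 1 = 3.
- Door-to-door: 0.

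**3. The plan's own figure** (section 5.A: 300 per arm before clustering, 10 clusters per arm, intraclass correlation 0.01, 5% missing)

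Children per cluster: m = 30 × (1 − 0.01) / (1 − 30 × 0.01) = 29.7 / 0.70 = 42.43.
Per arm: 10 × 42.43 = 424.3, and 424.3 / 0.95 = 446.6.
The stated 446 is reproduced. The sample size is not in dispute. It fixes the yardstick: a 10-point difference between two pooled groups, with an effective 600 children each (2 × 300).

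**4. Size of the possible bias** (loss ℓ is assumed; the documents give none)

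True coverage is 60% of all eligible children in every arm. A fraction ℓ leaves the denominator in the affected arm, and none of those children would have completed.

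- Affected arm: observed = 0.60 / (1 − ℓ).
- Pooled, one of two equal arms affected: observed = [0.60 + 0.60 / (1 − ℓ)] / 2.

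| ℓ | Affected arm | Pooled, one arm affected | Pooled bias |
|---|---|---|---|
| 5% | 0.60 / 0.95 = 63.2% | 61.6% | 1.6 points |
| 10% | 0.60 / 0.90 = 66.7% | 63.3% | 3.3 points |
| 15% | 0.60 / 0.85 = 70.6% | 65.3% | 5.3 points |

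If both pooled arms lose the same fraction, the pooled figure equals the affected-arm column. The full 10 points then needs ℓ = 1 − 0.60 / 0.70 = 14.3% in both arms.

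If a share q of the lost children would have completed, the affected-arm bias is ℓ(0.60 − q) / (1 − ℓ). It is largest at q = 0 and vanishes at q = 0.60.

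**5. Effect on the test** (600 v 600 effective; two-sided 0.025 per test, assumed as the correction for two tests, so z = 2.241)

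With d the pooled bias, p̄ the mean of 0.60 and the observed value, and SE = √[2p̄(1 − p̄) / 600], the chance of a significant result with no true difference is Φ(d/SE − 2.241) + Φ(−d/SE − 2.241).

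| ℓ | One arm affected: d, SE, chance | Both arms affected: d, SE, chance |
|---|---|---|
| 5% | 0.0158, 0.0282, 5% | 0.0316, 0.0281, 13% |
| 10% | 0.0333, 0.0281, 15% | 0.0667, 0.0278, 56% |

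The nominal chance is 2.5%.

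**The case against.** A reader might infer that the protocol has parents told their method at the meetings, before the census, and computes coverage on denominators that differ by arm. The documents do not support that as fact.

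- The English meetings are with leaders, and the sentence about parents carries no date. It can be read as an instruction for distribution days. The explanation to family heads is of the protocol and is not said to disclose the allocation.
- The Census and randomization section describes the census before the village randomisation. The Table 1 row may refer to randomising sub-districts to start years.
- The census aims at all households with children under 5, which limits arm-dependent listing at the start. Section 5.C adds a census update at the end of the season, which may recover children missed earlier.
- Under the French text, a caregiver who refuses SMC could stay on the list and count as uncovered. A caregiver who dislikes the fixed point, which is in the village, can also consent and simply not attend. That child remains in the denominator as uncovered.

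These points stand, and they reduce the concern to a risk. They do not remove it: no text conceals allocation before consent, later-round consent necessarily follows it, and the denominator is left open.

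Two further stronger readings also fail. Setting the 3 to 11 points of the affected arm against the 10-point design difference is valid only if both pooled arms are affected; with one affected, the bias is half that. Nor does the argument carry to Year 2, which uses a single delivery method and has incidence as its outcome.

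**Conclusion.** The concern holds as a risk that the protocol permits and does nothing to prevent: Year 1 coverage can be computed on arm-dependent denominators. The likelier routes are individual consent, entry at later rounds and, in the French text, consent to the survey itself. Arm-dependent listing at the first census is less likely.

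In the assumed worst case, the bias is about 3 to 11 points in an affected arm and about 1.6 to 5.3 points in the pooled comparison when one of its two arms is affected. This rests on an assumed loss of 5% to 15%, no loss elsewhere, and no completion among the lost children. Real bias would be smaller if some of them would have completed, and absent if coverage is in fact taken over all listed eligible children. The change is worth making because it is cheap and the loss cannot be repaired at analysis.

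**What to change.** For Year 1:

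1. Hold the community meetings in method-neutral terms. Complete the household census and individual consent, lock the list, and only then draw or announce the village allocation.
2. State that the sampling frame and denominator for coverage are all listed eligible children, including those under 3 months at census who age in by date of birth. Count refusers as not covered, at least in a sensitivity analysis.
3. Children first found at a later round stay in the study as planned but are left out of the primary coverage denominator.
4. Reconcile the English text (written consent for inclusion) with the French (oral for SMC, written for the surveys), because the two imply different denominators.

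The cost is a reordering of activities already planned, one short message to villages after the draw, and slightly less time to prepare fixed points before August.

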#### ***Census and randomization***

Once community consent to the trial is obtained, a household census will be conducted and all households within the study areas with children under 5 years of age will be identified. At the time of census, a preliminary screening of potentially eligible children will be undertaken. Eligible children will be identified and written informed consent will be obtained from their caretakers for their inclusion in the trial. Children entered into the trial will be assigned a unique ID number and their demographic data (date of birth and/or age, and gender) will be collected.

The census will be updated at each SMC round and potentially eligible participants (such as children who did not reach the age of three months during the previous round) will be identified and screened for eligibility and enter into the study. This updated census will collect information on migration and death of children enrolled into the study for precise estimation of person-time of follow-up.

The unit of randomization will be village and all eligible children in a village will be allocated to the same study arm (DDD+ DOT or DDD+NDOT or FPD+ DOT or FPD + NDOT) to avoid confusion in Year 1. Villages in the selected sub-districts will be randomized at 1:1 ratio to receive either a door –to-door delivery (DDD) or fixed point distribution (FPD) of SMC. They will also be randomized to receive SMC as directly observed therapy (DOT) or a non-directly observed therapy (NDOT). In Year 2, villages in the two newly randomly selected districts will be randomized into two groups to receive either three or four rounds of SMC.

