### **General Description of Study Design and Methods:**

The design is a cluster-randomized trial over three years. The target population is children aged 3-59 months old living in Ouelesseboungou district, Mali. In Year 1, villages in four sub-districts will be randomized into four groups (FPD+DOT; FPD+NDOT; DDD+DOT; DDD+NDOT). The optimal mode of delivery will be selected based on the SMC coverage during the first year,

and will then be implemented in villages of two additional sub-districts. Villages in these two sub-districts will be randomized in two groups. Children in the first group will received three rounds of SMC and those in the second group will receive four rounds of SMC to determine the optimal frequency of SMC based on the incidence rate of clinical malaria as measured by passive surveillance. Children in the four sub-districts selected in Year 1 will continue to receive three rounds of SMC in Year 2 using the optimal mode of delivery. In Year 3, children in the randomly selected sub-districts will received SMC by the optimal delivery system determined in Years 1 -2. Immune responses will be measured and compared between the children receiving SMC to a cohort of children not receiving SMC, to assess the impact of SMC on key antimalarial antibody responses over the three year period using cross-sectional surveys at the beginning and the end of the transmission season. Prevalence of malaria infection, anemia and molecular markers of *P. falciparum* resistance to SP and AQ will be measured during these cross-sectional surveys as secondary endpoints in randomly selected sample of the children.

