## 5. Statistical Considerations and Data Analysis

### A. Sample Size and Power Calculation(s)

*Cross-sectional surveys.* Sample size for cross-sectional surveys will be based on the SMC coverage. Assuming 60% average coverage of SMC by the combination of nonoptimal methods (pools of two groups), 300 children/arm will be needed to detect 10% increase in average coverage for two pooled groups with at least 85% power correcting for multiple tests and using two Fisher's exact tests. To account for cluster sampling with a minimum 10 clusters per arm, interclass correlation of 0.01 (based on a previous trial showing vaccine coverage (Dicko et al BMC Pub Health 2011), and 5% missing data, 446 children will be surveyed per group (total of 1784 children).

*Passive surveillance.*

Assuming a clinical malaria attack rate of 0.3 per child per year in “3 rounds” arm, to detect an absolute difference in attack rate of the 0.075 episode/chil/ year (corresponding to 25% reduction) in the “4 rounds” arm, with a one sided p-value of 0.025 and power of 80%, using a quasi poisson model accounting for 20 equally sized clusters per arm with intraclass correlation of 0.01 and 5% missing data we will need 1386 per arm, or 2,772 subjects total.

*Immunological parameters.* We will base our sample size calculations for immunological endpoints on the humoral immune response to AMA1. We select this response because AMA1 is highly immunogenic from among malaria antigens. Also, the intervention in this trial is directed at reducing the blood stage burden of parasites during the malaria season, and the response to AMA1 reflects exposure to blood stage forms of the parasite. In earlier serology studies of young children participating in an AMA-1 vaccine trial in Bancoumana, Mali (Sagara et al, Vaccine, 2009), we observed the peak antibody titer against AMA1 to occur near the end of the malaria season (among children receiving control vaccine), with geometric mean antibody levels of 120 antibody units (95% CI, 70-205). Antibody levels just prior to the start of the malaria season (before vaccination) were 40 (25-75) antibody units. Based on these data, 467 subjects per

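### Village randomization states no restriction by sub-district and the listed analyses have no sub-district term, so avoidable chance variation remains, mainly in the Year 2 comparison

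*Protocol*

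**What the plan says.** Protocol, Census and randomization, fixes the unit: "The unit of randomization will be village and all eligible children in a village will be allocated to the same study arm". For Year 1 it then says "Villages in the selected sub-districts will be randomized at 1:1 ratio" to door-to-door or fixed-point delivery, followed by "They will also be randomized to receive SMC as directly observed therapy (DOT) or a non-directly observed therapy (NDOT"). The second sentence gives no ratio and no link to the first. The protocol summary puts the same step as "villages in four sub-districts will be randomized into four groups". For Year 2, villages in the two newly selected "districts will be randomized into two groups to receive either three or four rounds of SMC". The French version (section 4.4) reads the same way. Neither version mentions stratification, blocking or another restriction by sub-district, and neither says the allocation is unrestricted.

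The sample-size section assumes, for the Year 1 survey, an ICC of 0.01 "with a minimum 10 clusters per arm". For Year 2 it assumes 20 equal clusters per arm and the same ICC. The Year 1 number of villages is not given.

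The Final Analysis Plan adjusts coverage for the cluster design. It adjusts incidence for age, previous SMC regimens and repeated episodes in the same child. Sub-district is not on either list.

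**The concern.** The French text calls the sub-districts aires de santé, that is, health areas. Clinical malaria is found passively by health-centre staff and community health workers (Follow-up and measurement of outcomes). Both the true rate and the share of cases detected can therefore differ between sub-districts.

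Year 2 is the most exposed because only two sub-districts hold all the villages. If one arm draws more villages from the higher-rate sub-district, the arm difference moves for a reason unrelated to the number of rounds. That difference decides how many rounds all children receive in Year 3, and the protocol calls 7.5 episodes per 100 children per year meaningful. Nothing in the stated allocation prevents such a split, and nothing in the stated model removes it.

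In Year 1 there is the further question of whether the four arms come out equal, since the survey size assumes at least 10 villages in each.

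**Working it through.** **1. Year 2: chance of an uneven split.** Inputs: 20 villages per arm, hence 40 (sample-size section). An equal division of 20 villages per sub-district is my assumption. With equal arms and no stratification, the number of four-round villages in one sub-district is hypergeometric (40, 20, 20), with mean 10 and SD 1.60.
- P(12:8 or worse) = 0.343
- P(13:7 or worse) = 0.113

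**2. Year 2: size of the shift.** With sub-district rates a and b, a 12:8 split against 8:12 moves the arm difference by (12/20 − 8/20) × |b − a| = 0.2 × |b − a|. The documents give no gap between sub-districts, so I show a range, centred on the stated 0.3 per child-year.

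| Assumed gap | Rates | Shift at 12:8, per 100 | Share of 7.5 |
|---|---|---|---|
| 1.25-fold | 0.267 v 0.333 | 1.3 | 18% |
| ICC ceiling (about 1.45-fold) | 0.245 v 0.355 | 2.2 | 29% |
| Twofold | 0.20 v 0.40 | 4.0 | 53% |

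The ICC ceiling takes the variance as about 0.3 (Poisson assumption). Between-village variance is then 0.01 × 0.3 = 0.003, SD 0.055. If all of it lay between the two sub-districts, their rates would be 0.3 ± 0.055. A twofold gap needs a between-village variance of 0.10² = 0.01, an ICC of about 0.01/0.3 = 0.03, three times the stated value.

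**3. Year 2: is this already in the ICC?** At the ceiling, the SD of the shift over all allocations is (1.60/10) × 0.11 = 0.0175. The between-village part of the standard error that the plan budgets is √(2 × 0.003/20) = 0.0173. These agree, so up to that gap the sample size already pays for the variation. Stratifying would recover it as precision.

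**4. Year 1: the plan's own figure.** n = 300 × (1 − 0.01)/(1 − 300 × 0.01/10) = 297/0.70 = 424.3, and 424.3/0.95 = 446.6. The stated 446 per group is reproduced.

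**5. Year 1: pooled power.** The powered test pools two arms: 600 v 600 effective children, 60% v 70%, two-sided 0.025 per test (assumed, since the multiplicity correction is not specified). Power is 0.919. With k villages and 424 usable children, the effective number per arm is 424/(1 + (424/k − 1) × 0.01).
- Arms of 7 and 13 villages within a pooled group: 265.7 + 322.2 = 587.9, power 0.913.
- Seven villages in every arm: 265.7 per arm, power 0.88.

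Both stay above the stated 85%.

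**6. Year 1: four-arm counts.** Suppose the two factors were drawn separately, each exactly 1:1. At 40 villages, P(10 in every arm) = C(20,10)²/C(40,20) = 0.248. P(every arm at least 10) is 0.85 at 48 villages, 0.95 at 52 and 0.996 at 60.

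**7. Year 1: area balance.** With equal but unstratified arms and four equal sub-districts (assumed), some arm is absent from a sub-district in 43% of allocations at 40 villages, 10% at 60 and 2% at 80.

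**The case against.** The strongest reply is that the text is silent, not wrong. A reader might infer two separate, unrestricted draws. The documents do not say so: the summary's four groups and the four named combination arms both fit one joint allocation, and the sentence on observed treatment is ordinary wording for a two-factor design. That stands. The defensible statement is that no restriction is stated. Details of allocation lists and model terms can also sit in a plan that is not shown. However, this protocol describes its allocation and lists its adjustments, and restriction must be settled before villages are allocated.

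A reader might also infer that Year 1 power is at risk. It is not: the powered comparison is pooled and hardly moves. Two exact 1:1 draws keep each factor's margin balanced in every case. The 10-village minimum is a sample-size assumption for the Year 1 survey only.

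A third tempting reading is that area imbalance could take up half the Year 2 target. That needs a twofold gap between sub-districts, which appears nowhere in the documents and does not fit the stated ICC. Chance imbalance under randomization also adds variance, not systematic bias.

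Finally, stratification alone does not guarantee equal arms. With 10 villages in each of four sub-districts and blocks of four, two villages are left over in each. If the leftover pairs are assigned independently, all four arms reach 10 in only 90/6⁴ = 90/1,296 = 7% of allocations. This stands, and the fix has to allow for it.

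**Conclusion.** The point holds as a modest design improvement. As written, the protocol leaves sub-district out of both the allocation and the listed models. In Year 2, a 12:8 or worse split has probability 34% if the 40 villages divide 20/20 by sub-district. Such a split moves the rate difference by about 1.3 to 2.2 per 100 for gaps from 1.25-fold up to the ceiling that ICC 0.01 allows, against a target of 7.5. A 4 per 100 shift requires an ICC of about 0.03. All of this is avoidable variance.

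In Year 1 the effect on pooled coverage power is negligible (0.919 to 0.913). Unequal four-arm counts matter only if there are few villages, and the total is not stated: they are a real possibility near 40 and practically absent at 60 with exact draws. Four-way comparisons are more exposed to area imbalance than the pooled ones.

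**What to change.** In Census and randomization, state the number of villages. For Year 1, specify one joint 1:1:1:1 allocation of villages to the four named arms; for Year 2, one 1:1 allocation to three or four rounds. Stratify each by sub-district, and assign villages left over within a stratum under an overall constraint that keeps arm totals equal. Make the matching change in the French section 4.4.

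In the Final Analysis Plan, add sub-district as a fixed effect in the coverage and incidence models, so that the analysis follows the stratified design.

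The cost is a slightly more complex allocation list and degrees of freedom: three for four sub-districts in Year 1 and one for two in Year 2. There is no field cost if the change is made before allocation. If allocation has already taken place, the fixed effect can still be added and the split of villages by arm and sub-district reported.
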